#### Secondary Objectives

The secondary objectives are as follows:

To predict the outcomes and prognosis of placental dysfunction–related complications by applying the developed predictive modelsTo evaluate the predictive value of clinically tested pregnancy biomarkers for pregnancy outcomes related to placental dysfunctionTo investigate placental biological processes and their role in generating maternal circulating biomarkers associated with preeclampsia and FGR, thereby enhancing the understanding of uteroplacental dysfunction pathophysiology

### Study Population

Pregnant individuals presenting for clinical screening visits at the MFM unit, GCUH, are considered potentially eligible participants.

#### Inclusion Criteria

Participants are eligible for inclusion if they are aged ≥18 years, have a singleton pregnancy, have a gestational age <37 weeks at recruitment, and are able to read and provide written informed consent.

#### Exclusion Criteria

Participants are excluded if they have a multiple pregnancy; a pregnancy complicated by a major fetal anomaly, chromosomal abnormalities, or genetic syndromes; or preexisting maternal cardiac disease (including cardiomyopathy, heart failure, valvular disease, and ischemic heart disease).

### Ethical Considerations

#### Ethics Approval

This study received ethics approval from the Gold Coast Hospital and Health Service Human Research Ethics Committee (HREC/2022/QGC/84257) and the Griffith University Ethics Committee (2022/254). Any proposed amendments or substudies to the protocol will be reviewed and approved by the Study Steering Committee to ensure ongoing compliance with ethical standards.

#### Informed Consent

All participants provide written informed consent prior to enrollment. Participation is voluntary, and participants can withdraw at any time without impact on their current or future clinical care and may request the destruction of their previously collected data and samples.

#### Privacy and Confidentiality

All data and biospecimens are deidentified at collection using unique study IDs. Study data are collected and managed using REDCap (Vanderbilt University), a secure web-based platform hosted at Griffith University, in a reidentifiable format [30]. Biospecimens are stored in a reidentifiable format at –80 °C in the Pregnancy Research Laboratory at Griffith University. Access to study data and biospecimens is restricted to authorized research personnel only. All published data will be deidentified and presented in aggregate, ensuring participant confidentiality.

#### Compensation

No financial compensation is provided to study participants, as all study procedures are integrated into routine antenatal care and require no additional hospital visits. In addition, no costs are incurred by participants for study-related measurements.

### Recruitment and Retention

The recruitment strategy aligns with routine clinical visits at GCUH during 3 gestational periods of 11 to 13 weeks, 26 to 28 weeks, and 35 to 36 weeks. Women may join the cohort at any stage before 37 weeks of gestation. To facilitate the collection of longitudinal data and samples, participants enrolled in early to midgestation are encouraged to continue participation through delivery. Primary recruitment focuses on pregnant individuals attending the combined first-trimester screening at the MFM unit and includes referrals from all models of maternity care at Gold Coast Hospital and Health Service. Eligible women admitted to the GCUH maternity ward are also considered for inclusion. Clinical staff within the assessment units have been trained in the study protocol and eligibility criteria to ensure accurate information dissemination to potential participants. Eligible women expressing interest are approached by research midwives and clinic investigators for a detailed discussion of the study.

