**Methods:**

The Placental Health Study is a prospective cohort study conducted at the Maternal Fetal Medicine Unit at Gold Coast University Hospital, Australia. Singleton pregnancies are enrolled at 11 to 13 weeks, 26 to 28 weeks, and 35 to 36 weeks of gestation and are followed until delivery. Exclusion criteria are multiple pregnancies, major fetal anomalies, maternal age below 18 years, and inability to provide informed consent. Clinical data, standardized ultrasound and Doppler measurements, hemodynamic parameters, and biospecimens (serum, plasma, whole blood RNA, and urine) are collected at each visit. Three gestational age-specific datasets (11‐13 weeks, 26‐28 weeks, and 35‐36 weeks) will be constructed for model development. Prediction models will be developed using multivariable logistic regression. Competing risks (Fine and Gray) models will be used as sensitivity analyses for outcomes related to gestational age at delivery. Bayesian updating will be applied to refine existing Fetal Medicine Foundation risk estimates using additional biomarkers or variables collected later in pregnancy. Developed models will undergo internal validation via 5-fold cross-validation, with performance assessed through model discrimination, calibration, and comparison against existing approaches. Collected biospecimens will also be analyzed for angiogenic markers and exploratory omics studies.

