#### Demographic and Clinical Data

Maternal demographic characteristics, medical and obstetric history are collected by research midwives, sonographers, and clinical research fellows at enrollment through face-to-face conversations or electronic medical records. Maternal risk factors are recorded in accordance with the National Institute for Health and Care Excellence (NICE) [33] and American College of Obstetricians and Gynecologists (ACOG) guidelines [34]. Clinical data, including routine ultrasound screenings, laboratory tests, and maternal and perinatal outcomes, are obtained from integrated electronic medical records.

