#### Sample Size Estimation

We estimate a 10% to 15% participation rate from the approximately 5000 annual deliveries at GCUH. On the basis of a prevalence of 10% for placental dysfunction–related disorders (preeclampsia and SGA or FGR), approximately 200 cases with these outcomes are expected. In the development of prediction models using binary outcomes (high-risk or low-risk) with a 10% incidence rate and up to 15 predictors, targeting an area under the receiver operating characteristic curve (AUC-ROC) of 0.75, the estimated sample size is approximately 1700 participants [42].

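### The one planned size of about 1700 is what a single model needs; three window-specific models are planned under staggered entry, and none can contain more than 1216 women

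*Protocol article*

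**What the plan says.** The Abstract describes entry in three windows: "Singleton pregnancies are enrolled at 11 to 13 weeks, 26 to 28 weeks, and 35 to 36 weeks of gestation". It then says that one dataset will be built for each window. The section on prediction model development fits a multivariable logistic model at each window.

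The entry rules are wider. The Inclusion Criteria require only that women "have a gestational age <37 weeks at recruitment". Recruitment and Retention first says "The recruitment strategy aligns with routine clinical visits at GCUH during 3 gestational periods" and then "Women may join the cohort at any stage before 37 weeks of gestation". It adds a route that is not tied to any window: "Eligible women admitted to the GCUH maternity ward are also considered for inclusion". Staying on for later visits is not required: "participants enrolled in early to midgestation are encouraged to continue participation through delivery".

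Sample Size Estimation assumes a 10% incidence, up to 15 predictors and an AUC of 0.75, and concludes that "the estimated sample size is approximately 1700 participants". It does not divide this figure by window or by outcome. The Results report that recruitment closed in February 2026 with 1267 enrolled, of whom 1072 had completed pregnancies, 144 were still pregnant, and 51 had withdrawn or had missing or duplicated data. No count per window is given.

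**The concern.** A sample size for a prediction model belongs to the dataset in which that model is fitted. Here there are three datasets and one number. A woman who first joins at 35-36 weeks has no study visit at 11-13 weeks, and a woman who joins early need not attend later. The enrolled total is therefore an upper limit for each window, not its size. A reader who sets 1267 against 1700 learns how far recruitment fell short, but not how well any of the primary models is supported.

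A second, conditional risk concerns the earlier windows. Routine data come from records: "Clinical data, including routine ultrasound screenings, laboratory tests, and maternal and perinatal outcomes, are obtained from integrated electronic medical records". The Discussion says that Fetal Medicine Foundation (FMF) first-trimester screening is routine at this hospital. Many later joiners may therefore have 11-13-week values on file. If such a woman were placed in the 11-13-week dataset, she would be counted as at risk from the first trimester, although she could enter the study only because she was still undelivered weeks later. Primary objective 1 concerns preterm preeclampsia, which is defined by delivery before 37 weeks, so this selection acts directly on the outcome.

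**Working it through.** **Inputs.** From Sample Size Estimation: incidence 10%, P = 15 predictors, AUC 0.75, stated size about 1700. From the Results: 1267 enrolled, 51 withdrawn, missing or duplicated. Assumed, because the article does not give it: target shrinkage S = 0.90, the usual default of the minimum-sample-size criteria for prediction models.

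**Step 1: reproduce the plan's figure.**
- An AUC of 0.75 at 10% incidence, with a normally distributed linear predictor, corresponds to a Cox-Snell R² of 0.0747 (by simulation).
- The shrinkage criterion is n = P / [(S − 1) × ln(1 − R²/S)].
- With the numbers in: n = 15 / [(−0.10) × ln(1 − 0.0747/0.90)] = 1731.
- The other criteria ask for less: 596 (optimism in R²), 398 (mean absolute prediction error of 0.05) and 138 (overall risk).
- 1731 is within 2% of 1700 (1731/1700 = 1.018). The stated size is therefore what one model in one dataset needs.

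**Step 2: the most that any window can hold.**
- 1267 − 51 = 1216 women, even if every remaining woman counted in every window.
- 1216/1700 = 72%. The shortfall is 1700 − 1216 = 484, or 28%.
- Events at 10%: 1216 × 0.10 ≈ 122, or 122/15 ≈ 8.1 per predictor. At 1700 it would be 170/15 = 11.3.
- Solving the Step 1 formula for S at n = 1216 gives an expected shrinkage of 0.864, against about 0.90 at 1700.

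**Step 3: smaller windows.** The share of women in each window is not reported. As an assumed range applied to 1216:

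| Share in a window (assumed) | Women | Share of 1700 |
|---|---|---|
| 80% | 973 | 57% |
| 50% | 608 | 36% |
| 33% | 405 | 24% |

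Expected shrinkage from the same formula is 0.81 at 800 women, 0.76 at 600 and 0.68 at 400.

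**Step 4: which windows staggered entry reduces.** The 11-13-week dataset loses everyone who joins later, unless their values come from records. The 35-36-week dataset can gain women carried forward from earlier windows, so it may lose little to staggered entry. It does lose women who deliver or leave before then.

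**Step 5: direction of the conditional bias.** A woman first enrolled at 35-36 weeks cannot have delivered with preeclampsia before she entered. Adding such women to an earlier dataset enlarges the denominator and adds only the few cases delivered between entry and 37 weeks. Observed incidence falls, and absolute risks fitted to that dataset would tend to be too low. Its size cannot be estimated from the article, because entry by gestation is not given.

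**The case against.** Several objections are fair and limit the point.

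- **Cause of the shortfall.** A reader might infer a choice between undersized windows and back-filled ones. The figures do not support that: at 1216, even back-filling everyone leaves every window below 1700. Under-recruitment comes first, and staggered entry adds to it.
- **Back-filling is not planned.** A reader might infer that late joiners will be entered as event-free survivors. The article does not say so. Gestational age-specific datasets read most naturally as women assessed in that window. The study's PlGF and sFlt-1 measurements come from collected samples, which a late joiner lacks for earlier windows. The FMF first-trimester risk is used as the prior at later windows, but that is sound for a woman who is at risk from the later window onwards. The bias therefore remains a conditional risk.
- **The entry wording.** Elsewhere the article uses stage for the three windows, so joining at any stage may mean any of the three. Counting the calendar weeks outside the windows says nothing about how many women entered there, and the article says that primary recruitment focuses on first-trimester screening. The ward route still allows off-window entry, in unknown numbers. Ward admissions may also deliver soon with preeclampsia, which would partly offset the fall in incidence.
- **Detail left to the analysis plan.** Dataset-membership rules commonly sit there, and their absence here is no fault. The article does, however, state a size, three models and a final enrolment, and these do not fit together.

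**Conclusion.** The point holds as a sample-size point with a conditional safeguard attached. The stated size is the need for one model, and no window model can reach it: at most 1216 women, 72% of 1700, with about 122 events and an expected shrinkage of about 0.86. Reading the figure as a single-model requirement rests on the assumed shrinkage target of 0.90. The ceiling rests on removing all 51; keeping them would give 1267, or 75%.

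The ceiling is also favourable in another respect. The 10% refers to preeclampsia and SGA or FGR combined, while the objectives name narrower outcomes such as preterm preeclampsia, which will have fewer events.

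How far each window falls below 1216 cannot be known from the article. Nothing shown establishes that back-filling has been or will be done, so no bias can be claimed, only that nothing in the text prevents it.

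**What to change.** 1. Restate the figure of about 1700 as a requirement for each window model, for the outcome and number of predictors it assumes.
2. Report participants and events per window beside the 1267, and state the lower precision (expected shrinkage, events per predictor) that the achieved numbers allow.
3. Define each window dataset as women enrolled in or before that window, with index measurements taken within it, and still at risk at that time. First-trimester values from records may still serve as predictors or as the prior in a later window, but should not place a woman in a dataset earlier than her enrolment.
4. Keep women who entered between windows for the biobank and longitudinal work.

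This takes wording and a filter on enrolment and measurement dates already held. The main publications are still to come, so it can be done now. The price is that smaller and less favourable model sizes are reported.

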### Definitions of Preeclampsia and FGR

The diagnosis of preeclampsia follows the 2021 International Society for the Study of Hypertension in Pregnancy guideline [31]. Preeclampsia cases are subclassified based on gestational age at delivery as preterm preeclampsia (delivery <37 weeks) or term preeclampsia (delivery ≥37 weeks) [31]. FGR is defined in the absence of congenital anomalies according to international Delphi consensus criteria, with distinctions between early-onset and late-onset presentations (Textbox 1) [32].

Textbox 1.Definitions of early- and late-onset fetal growth restriction [32].

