### Study Objectives

#### Primary Objectives

The primary objectives of this study are as follows:

To improve current predictive models or develop new predictive models for placental dysfunction–related pregnancy complications, including preterm preeclampsia and FGR, at 2 critical gestational periods: the first trimester (11‐13 weeks) and the second trimester (26‐28 weeks)To establish third-trimester (35‐36 weeks) models to predict term preeclampsia and FGR and to define the optimal time for delivery.

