**Late-onset fetal growth restriction: gestational age ≥32 weeks**
Abdominal circumference or estimated fetal weight <3rd percentileORAt least 2 of the following 3:Abdominal circumference or estimated fetal weight <10th percentileAbdominal circumference or estimated fetal weight crossing >2 quartiles (50 percentiles) on growth charts (growth centiles are noncustomized)Cerebroplacental ratio <5th percentile or umbilical artery pulsatility index >95th percentile

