Ultrasound and Doppler	Fetal biometry (BPD^p^, HC^q^, AC^r^, FL^s^, EFW^t^, and DVP^u^); biophysical markers (cervical length and measurement method and placenta position); fetal Doppler (umbilical diastolic flow, UA^v^ PI Dopplers, MCA^w^ PI Dopplers, ductus venosus A-wave, and ductus venosus Dopplers-PIV^x^); and maternal Doppler (right and left uterine artery pulsatility index and mean PI)
Maternal hemodynamics	Systolic BP, diastolic BP, MAP, augmentation index, and maternal ophthalmic artery Doppler (right and left PI, RI^y^, EDV^z^, PSV^aa^-1, PSV-2, and PSV-2:PSV‐1)
Biochemical markers	PlGF, sFlt-1, and sFlt-1:PlGF ratio
Clinical pathology	Urine test, full blood count, chemistry panel, and recent iron infusion date (if available)
GDM screening	Random glucose, HbA_1c_^ab^, OGTT^ac^ (fasting, 1-hour, and 2-hour values); and insulin or metformin use
At delivery	
Delivery details	Gestational age at delivery; onset of labor; type of rupture of membrane; PPROM^ad^; FBS^ae^ test results; delivery type; number of vessels in cord; antenatal, intrapartum, and postnatal blood loss; postpartum hemorrhage
Neonatal outcomes	Live birth or stillbirth, onset of respirations, birth weight, birth length, head circumference, sex, Apgar scores (1 and 5 minutes), resuscitation, cord gas analysis, and SCN^af^ or NICU^ag^ admission
Maternal outcomes	BP, postpartum hemorrhage, and adverse events
All visits	
Pregnancy complication and medication	Preeclampsia, GH^ah^, antepartum hemorrhage, threatened preterm labor, FGR, PPROM, GDM^ai^; gestational age at diagnosis; medication details (start and stop date and dose)
Biological sample collection	Plasma, serum, whole blood (in PAXgene RNA blood tube), and urine

a FGR: fetal growth restriction.

b NICE: National Institute for Health and Care Excellence.

c ACOG: American College of Obstetricians and Gynecologists.

d NIPT: noninvasive prenatal testing.

e cfDNA: cell-free DNA.

f CRL: crown-rump length.

g NT: nuchal translucency.

h PI: pulsatility index.

i FHR: fetal heart rate.

j BP: blood pressure.

k MAP: mean arterial pressure.

l hCG: human chorionic gonadotropin.

m PAPP-A: pregnancy-associated plasma protein A.

n PlGF: placental growth factor.

o sFlt-1: soluble fms-like tyrosine kinase-1.

p BPD: biparietal diameter.

q HC: head circumference.

r AC: abdominal circumference.

s FL: femur length.

t EFW: estimated fetal weight.

u DVP: deepest vertical pocket.

v UA: umbilical artery.

w MCA: middle cerebral artery.

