This project aims to enhance existing prediction models for term preeclampsia and SGA through the evaluation of additional biomarkers across 3 critical gestational stages, investigating both routine antenatal measurements and specialized markers of placental and cardiovascular dysfunction, including Doppler ultrasound parameters, maternal hemodynamic indices, and angiogenic markers. Doppler ultrasound assessment of uterine arteries can reflect placental perfusion status, with elevated values indicating increased resistance and impaired placental blood flow [57,58]. Maternal hemodynamic parameters, including ophthalmic artery Doppler indices, MAP, and augmentation index, provide insights into cardiovascular adaptation and peripheral vascular function [59-61]. Angiogenic markers (sFlt-1, PlGF, and the sFlt-1:PlGF ratio) indicating angiogenic imbalances serve as biochemical predictors of placental dysfunction [20,62,63] and spontaneous preterm labor [64]. Furthermore, our study establishes a valuable biobank for identifying novel molecular biomarkers and investigating underlying mechanisms of placental dysfunction through omics techniques. Incorporating these diverse markers and novel biomarker candidates into existing prediction models has the potential to enhance accuracy for late-onset pregnancy complications.

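### The 35-36 week model predicts term FGR, but FGR is defined only by ultrasound and no study scan follows, so later FGR is recorded only in women who happen to be scanned again

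*Protocol article*

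**What the plan says.** Under Definitions of Preeclampsia and FGR, the article states that "FGR is defined in the absence of congenital anomalies according to international Delphi consensus criteria". For late-onset disease, Textbox 1 lists abdominal circumference or estimated fetal weight centiles, centile crossing on growth charts, and "Cerebroplacental ratio <5th percentile or umbilical artery pulsatility index >95th percentile". All are antenatal scan measures, and birth weight plays no part.

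The second primary objective is to establish 35-36 week "models to predict term preeclampsia and FGR and to define the optimal time for delivery". The Discussion repeats that the third-trimester model concerns the onset of term complications.

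On timing, "The recruitment strategy aligns with routine clinical visits at GCUH during 3 gestational periods", the last being 35-36 weeks. Table 1 then moves straight to delivery. The Compensation section says the study needs no extra hospital visits, and Demographic and Clinical Data says routine ultrasound and perinatal outcomes come from electronic medical records. At delivery the study records "Live birth or stillbirth, onset of respirations, birth weight, birth length, head circumference, sex", together with gestational age at delivery.

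The growth outcome is named differently elsewhere. Sample Size Estimation counts "disorders (preeclampsia and SGA or FGR"), and the Discussion says the project aims to "enhance existing prediction models for term preeclampsia and SGA". Only FGR is defined.

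**The concern.** A model built at 35-36 weeks needs an outcome that can be established afterwards in every woman. Here the outcome needs a scan, and the last scheduled scan is the one that supplies the predictors. A fetus that becomes growth restricted after that visit is a recorded case only if somebody scans again. Otherwise the logistic model treats the pregnancy as a non-case, and the Fine and Gray sensitivity analysis places it in the competing event of delivery without the outcome.

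Two consequences need to be kept apart:

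- **Incomplete verification of any kind** lowers recorded incidence, and with it the predicted risk.
- **Selective verification**, where women with a small estimated weight, abnormal Dopplers or raised blood pressure are scanned more often, makes detection depend on the candidate predictors. Apparent discrimination and sensitivity may then rise above the truth.

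The planned cross-validation and calibration use the same labels, so they would not reveal either problem. The article justifies the study by the weakness of current models for late-onset disease, and this model is meant to inform delivery timing. Understated risk in women who are not flagged would matter there.

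**Working it through.** **1. The plan's own figures.** The article gives no re-scan rate and no performance figure for this model. Its sample size of about 1700 is reproduced by the shrinkage criterion n = P/[(S-1) ln(1-R²/S)]. With P = 15, S = 0.90 (assumed, the usual default) and R² = 0.0757 (derived from AUC 0.75 and 10% incidence), n = 15/(0.1 × 0.0879), about 1708. The present point does not affect that figure.

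**2. Definition against schedule.**

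| Item | Where | Content |
|---|---|---|
| Late FGR criteria | Textbox 1 | Ultrasound measures only |
| Predictor scan | Table 1, 35-36 weeks | Includes AC, EFW, umbilical and middle cerebral artery PI |
| Next scheduled study contact | Table 1 | Delivery, no scan |
| Extra study visits | Compensation | None |
| Known at every birth | Table 1 | Birth weight, sex, gestational age at delivery |

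The 11-13 and 26-28 week models are less exposed, because scheduled scans follow them.

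**3. Size, by illustration.** The 10% screen-positive rate is one of the article's examples. These inputs are assumed: true prevalence of later FGR 5%, true AUC 0.70, and the re-scan rates. The score is normal with unit variance in both groups, and cases are shifted by √2 × Φ⁻¹(0.70) = 0.742. Flagging the top 10% gives a true sensitivity of 27.7%. A case counts only if re-scanned.

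If re-scanning follows the score itself, at rate a in flagged and b in unflagged women:

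apparent sensitivity = s·a/[s·a + (1-s)·b]

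- 80%/20%: 0.277 × 0.8/(0.277 × 0.8 + 0.723 × 0.2) = 0.222/0.366, about 60%
- 60%/30%: 0.277 × 0.6/(0.277 × 0.6 + 0.723 × 0.3) = 0.166/0.383, about 43%

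The denominators, 0.37 and 0.38, are the shares of true cases detected. Simulation supplies the AUCs and the case in which re-scanning follows a clinical impression correlated 0.5 with the score (also assumed), with the top 10% on that impression re-scanned at the higher rate:

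| Re-scan rates, higher/lower group | Driven by | Observed AUC | Apparent sensitivity |
|---|---|---|---|
| all verified | – | 0.70 | 28% |
| 50%/50% | unselective | about 0.70 | 28% |
| 60%/30% | correlated impression | 0.72 | 32% |
| 80%/20% | correlated impression | 0.75 | 37% |
| 60%/30% | score itself | 0.75 | 43% |
| 80%/20% | score itself | 0.82 | 60% |

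In the unselective row, recorded incidence falls from 5% to 2.5%. When re-scanning follows the score, recorded risk in unflagged women is b times the truth. At the article's target AUC of 0.75, with rates of 80%/50% following the score, the observed AUC is 0.78 and sensitivity 46% against a true 34%.

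**The case against.** The article does not say who is scanned after 36 weeks. Table 1 records FGR and gestational age at diagnosis at all visits, and routine scans are imported from the records, so later diagnoses that are made will be captured. This stands: selective re-scanning is an inference, and with unselective re-scanning discrimination is not inflated. It does not remove the gap, because a fetus never scanned again yields no diagnosis to capture.

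Clinicians also cannot follow a score that did not exist while these women were under care. PlGF and sFlt-1 are still to be quantified in collected samples, with only a subset measured so far. This stands too. The lower rows of the table are an upper illustration, and the correlated case is more realistic.

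SGA may already be planned, since the article mentions it twice, and a condensed article may leave outcome derivation to a fuller document. That could settle how SGA is handled. It does not alter the stated FGR definition or schedule, which do not fit this objective.

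A reader might infer that SGA should replace Delphi FGR. The documents do not support that: the objective names FGR, and SGA would add constitutionally small babies and lose Delphi cases born above the 10th centile. A reader might also infer that centile crossing cannot be assessed in women who join at 35-36 weeks. Earlier routine scans in the records may supply it, and other criteria can be met at one scan.

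**Conclusion.** The concern holds for term FGR in the 35-36 week model. By the stated definition and schedule, later FGR in women not scanned again is counted as absence of FGR, so recorded incidence and predicted risk would be too low unless re-scanning is close to complete.

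Inflation of AUC and sensitivity is possible and probably present, but its size is unknown. Under the assumptions above it ranges from none (unselective re-scanning), through 0.02-0.05 in AUC and roughly 4-9 percentage points in sensitivity (moderate correlation), to 0.05-0.12 and roughly 15-32 points (re-scanning on the score). A reader might conclude that the reported performance will certainly be inflated. The documents do not support that, because they give no re-scan rates or reasons.

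The point should be fixed but is not critical to the whole study. It affects one outcome in one of three windows; the preeclampsia models and the sample size are untouched.

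**What to change.** For the 35-36 week growth model:

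1. Keep Delphi FGR as the named target.
2. Prespecify a co-reported outcome known at every birth: birth weight for gestational age and sex below the 10th centile, with below the 3rd as the severe category, on a named reference chart.
3. Report the proportion of women scanned again after the 35-36 week visit, by predicted-risk group.
4. Interpret Delphi FGR performance, including the Fine and Gray analysis, in the light of items 2 and 3.
5. Use FGR and SGA as distinct, defined terms throughout.

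No change to clinical scanning is implied. The cost is one derived variable from data already in Table 1, extraction of later scan dates from the records, and some extra reporting. Recruitment has closed, but the model publications are still to come, so this can be fixed beforehand. The birth-weight outcome includes constitutionally small babies and misses some Delphi cases born above the 10th centile, which is why it is added alongside Delphi FGR and does not replace it.
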